### Objectives

It is the goal of the present study to explore the efficacy of formally incorporating interventions on the distal causes of depression in the treatment of this condition. An evolutionary-driven cognitive therapy (ED-CT) protocol for depression is being developed and tested in this clinical trial. Thus, patients with depression initially complete a questionnaire aiming at identifying deficient areas of fitness, and are guided by the therapist on ways of improving on those areas. The therapeutic outcome will be compared with the outcome of a group of patients with depression undergoing a well-established CBT treatment, namely, Beck’s cognitive therapy (CT) for depression [27].

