#### The ED-CT group

The ED-CT group also undergoes a 1-hour session of therapy each week for 12 weeks. Therapy sessions follow the guidelines of the ED-CT manual that we have developed. Following implementation of the study, the manual will be available upon request from the first author, and will also be submitted for publication.

The ED-CT starts with the administration of a Fitness Evaluation Scale (FES), described below, which yields a comprehensive assessment of the client’s perceived darwinian or evolutionary fitness. The therapist thus begins the treatment with a clear understanding of the barriers to fitness that the patient is facing, in addition to the problems formulated by them at the beginning of therapy. In other words, the patient’s answers to the FES guide the evolutionary-driven intervention elements by providing additional focuses for treatment, alongside classic CT targets of intervention. Thus, the key difference between ED-CT and a classic CT approach is that in the ED therapy, the therapist comes pre-equipped with a list of fitness deficiencies identified by the patient through the completion of the FES at intake, which the therapist addresses alongside other problems.

The ED-CT intervention is based on standard CT while adding specific goals and techniques designed to increase an individual’s evolutionary fitness. We will succinctly describe the treatment course, focusing on the evolutionary aspects of the treatment.

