### Measures of other outcomes

For the first set of additional outcomes used in this study, the following measures are used.

• The FES is a scale adapted and expanded by the authors from the High-K Strategy Scale (HKSS) [50]. The HKSS has been shown to be negatively associated with depressive symptomatology [25] and psychopathology in general [23]. The FES consists of 45 items (58 if the patient has children), tapping into various dimensions theorized to make up the indicators of fitness. Participants rate every item on a five-point Likert scale. A total FES score is computed by adding up ratings for each item, with higher scores indicating greater fitness. The FES was preliminarily validated on a sample of 146 subjects, and showed good internal consistency (Cronbach’s α = 0.93). The FES is the therapist’s starting point in prescribing the evolutionary-driven interventions, as further detailed below.

• The Mate Value Inventory (MVI) [26] is a multivariate assessment of attributes desired in the self, and in social or sexual partners.The MVI is a list of 17 traits, for which participants are asked, ‘How well do you feel that these attributes apply to you currently,’ and are measured on a scale of -3 (extremely low on this trait) to +3 (extremely high on this trait). These traits are: ambitious, attractive face, attractive body, desires children, emotionally stable, enthusiastic about sex, faithful to partner, financially secure, generous, good sense of humor, healthy, independent, intelligent, kind and understanding, loyal, responsible, and sociable. Mate value is the summed score of these items. The MVI has been translated and adapted into Romanian for the purposes of the current study.

• The Components of Mate Value Survey (CMVS) [51] is a 21-item self-report measure. It is based on the Self-Perceived Mating Success Scale (SPMSS) [52], but in addition to the aspects of mate value indexed by SPMSS, it includes aspects related to sociality, parenting, wealth, looks, relationships history, and fear of failure. The CMVS has adequate reliability [26], and has been adapted into Romanian for the purposes of this study.

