### Data collection, management, and analysis

Each eligible patient is assigned a unique identification number and asked to complete the evaluation package, including the primary, secondary, and other outcomes, as well as demographic information (initial assessment). The same set of measures is administered after the final session (post-intervention assessment) and at 3 months after the final session (follow-up assessment). After sessions 4 and 8, patients also complete several measures of primary outcomes (that is, BDI-II), and other outcomes (ATQ, DAS, ABS II, PANAS, B-COPE, treatment outcome expectancies,WAI, CSQ-8, and Intent-to-Attend Scale). In addition, the participants complete the BDI-II, CSQ-8, and Intent-to-Attend Scale after each session.

To ensure high accuracy of data collection, all the measures are completed electronically, via a special system designed to reliably capture and organize the data points while minimizing the risk of missing responses. The system has been especially developed for the purposes of this study, and is secured on a server. Each participant uses their unique identification number to log on to the system. The therapists are responsible for assisting the patients in this process, and providing clarifications when needed.

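### CT patients also complete the FES at intake and therapists of either arm may assist, so CT therapists may be exposed to the fitness list that defines ED-CT: an unaddressed risk of partial contamination

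*Protocol article*

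**What the plan says.** All references are to the protocol article.

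- **Comparator.** Under Objectives, ED-CT is compared with patients "undergoing a well-established CBT treatment", namely Beck's CT. The CT group section describes CT without any FES content.
- **What separates the arms.** The ED-CT group section gives the key difference as follows: "the therapist comes pre-equipped with a list of fitness deficiencies identified by the patient through the completion of the FES at intake", and the therapist then works on that list alongside other problems. Measures of other outcomes calls the FES the therapist's "starting point in prescribing the evolutionary-driven interventions".
- **Who completes the FES.** Measures of other outcomes lists the FES first in the first set of additional outcomes. Data collection, management, and analysis says: "Each eligible patient is assigned a unique identification number and asked to complete the evaluation package, including the primary, secondary, and other outcomes". The same set is given again after the last session and at 3 months.
- **Who helps.** The same section, after describing log-on to the electronic system, says: "The therapists are responsible for assisting the patients in this process, and providing clarifications when needed".
- **Who the therapists are.** Assignment to interventions names four, two per protocol. Only the two ED-CT therapists received the extra training in the evolutionary components.

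**The concern.** The instrument that generates the experimental ingredient is completed in both arms, and the duty to assist is given to the therapists without restriction. Taken together, these rules allow a CT therapist to go through 45 to 58 fitness items with a CT patient and learn which areas the patient rates as deficient. CT is described as structured around goals, so a problem that has just come up could naturally become a target.

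This route carries experimental content into the control arm, so if it acts it reduces the difference that the superiority trial is meant to detect. A null result could then mean that fitness targeting adds nothing, or that some of it had reached the control arm. The Discussion makes this more than academic: it plans a further trial if ED-CT proves at least comparable with CT, and contamination would make comparability easier to reach.

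**Working it through.** **Step 1: does the text open the path?**

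1. The FES is one of the other outcomes (Measures of other outcomes).
2. Every eligible patient completes the other outcomes at the initial assessment (Data collection, management, and analysis). CT patients therefore complete the FES at intake. This is established.
3. Therapists assist and clarify, with no exception by arm, measure or visit (same section). Elsewhere the article calls the intake assessors clinical psychologists (Participant timeline, Recruitment) and reserves the word therapists for those who deliver treatment. Exposure of a CT therapist to a CT patient's FES is therefore permitted as written.
4. The article does not say whether the intake package comes before or after the patient meets the therapist, or who can view individual answers. Actual exposure is therefore possible but not shown.

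**Step 2: reproduce the plan's own sample size.** The inputs, from Sample size, are f = 0.247, m = 2 measurements, correlation ρ = 0.50, α = 0.05, two groups and N = 100. For a repeated-measures ANOVA, between factors:

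λ = f² × N × m / (1 + (m − 1)ρ) = 0.247² × 100 × 2 / 1.5 = 0.061009 × 133.33 = 8.13

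With a noncentral F on 1 and 98 degrees of freedom, power is 0.806. An N of 98 gives 0.798, so 100 is the smallest even total that reaches 0.80. The plan's figure reproduces.

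For the allocation obtained (43 CT, 57 ED-CT), the standardised difference on the mean of the two measurements is 2 × 0.247 / √0.75 = 0.570. Then λ = 0.570² × 43 × 57 / 100 = 7.98 (unrounded difference used), and power is 0.799.

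**Step 3: what an assumed dilution would cost.** The documents give no contamination rate, so the percentages are assumptions. The effect size f is multiplied by (1 − dilution), so λ is multiplied by its square.

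| Assumed dilution | f | λ at N = 100 | Power, 50:50 | Power, 43:57 | Total N for 80% power |
|---|---|---|---|---|---|
| 0% | 0.247 | 8.13 | 0.806 | 0.799 | 100 |
| 10% | 0.2223 | 6.59 | 0.720 | 0.711 | 122 |
| 20% | 0.1976 | 5.21 | 0.618 | 0.609 | 154 |
| 30% | 0.1729 | 3.99 | 0.507 | 0.499 | 200 |

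The table shows that the design has almost no reserve. It is not evidence that any dilution takes place.

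**The case against.** The strongest counter-argument is that the arms differ by the therapist's possession and use of the list, not by the patient filling in a form. Nothing in the article says that a CT therapist receives, reviews or acts on FES answers, or attends the intake assessment. The sentence about assistance follows the log-on text and may mean no more than practical help with the system. Mismatch-theory education, evolutionary conceptualization, FES-guided goals and FES-generated homework are described for ED-CT only, and only its two therapists had the extra training. A CT therapist who clarified an item would still lack the manual and the rationale. The article is also condensed, and access permissions are the kind of detail that a full protocol holds.

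Most of this stands, and it limits the point to a risk. A reader might infer that the comparator is no longer plain Beck CT, or that the contrast is in fact diluted. The documents support neither reading: they describe no FES review in the CT arm and give no rate of exposure.

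Two parts of the objection do not remove the point. First, this is not mere silence, because the article assigns the assisting role affirmatively and without limit. Second, therapist use of patients' responses is part of the design elsewhere. The intent-to-attend item is meant to alert therapists in both arms to problems, and the intake religiosity scale informs how ED-CT is presented.

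The same sentence also has unblinded therapists assisting with the self-reported BDI-II. That is a separate issue and could move the contrast either way, so the net direction of all bias is not established. Only the contamination route has a predictable direction.

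**Conclusion.** The point holds as a risk of partial contamination. Completion of the FES by CT patients at intake is certain from the text, and an unrestricted therapist role in assisting is stated. Exposure of CT therapists to the answers, and any use of them, is possible but not shown. If the route acts, it shrinks the ED-CT minus CT difference and makes a null result harder to interpret. It would not erase the difference, because training, rationale and FES-driven homework remain specific to ED-CT.

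The size is unknown. The power figures of about 0.72 and 0.62 rest wholly on assumed dilutions of 10% and 20%, and on the plan's own f, correlation and two-measurement ANOVA. The point merits a change because the remedy is cheap and the sample size leaves no margin. It does not justify describing the control arm as something other than CT.

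**What to change.** In Data collection, management, and analysis:

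1. Have the baseline package, FES included, completed before the research assistant links the patient to a therapist. Any help comes from the blinded intake psychologists or from on-screen text.
2. Set permissions in the electronic system so that individual intake FES answers are released only to ED-CT therapists.
3. At post-treatment and follow-up, have therapists of neither arm assist with the FES. Barring only the CT therapists would make collection of this outcome differ by arm.
4. For patients already treated, record whether the CT therapist assisted with or saw the intake FES, and report it with the results.

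The cost is small: a permissions setting in a system built for this study, a fixed order for one existing intake step, and slightly more work for the intake assessors. Treatment content, sample size and analysis are unchanged. One limit remains: FES completion itself stays common to both arms because it is an outcome, so any effect of merely answering the items is not removed.

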### Trial design

This study is designed to be a blinded, randomized, superiority clinical trial. The experimental group receives ED-CT, while the control group receives CT. We hypothesize that, because the intervention array is larger in the case of ED-CT, the therapeutic gains will be larger in this condition than in the CT group at the completion of the therapy, and that this will be maintained at the 3-month follow-up.

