### Outcomes and measures

#### Primary outcomes

The level of depressive symptomatology and a categorical diagnosis of depression after treatment constitute the primary outcomes.

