**CONSORT flow diagram**[94]**showing subject allocation to the therapy conditions.**

### Sample size

An *a priori* power analysis based on a medium effect size estimation indicated that a total of 100 participants are needed (planned main statistical test is ANOVA (repeated measures, between factors); *f* effect size: 0.247; statistical power: 0.80; α error probability: 0.05; two groups, two main measurements (pre-intervention and post-intervention); correlation between repeated measures: .50). Power analysis was computed using the G*Power 3.1.6 program [95]. Consequently, we randomized a total of 100 participants. Following generation of the random numbers, we decided to use the first sequence of numbers for the participants’ allocation to the groups. This resulted in 43 participants randomized to the CT group, and 57 participants randomized to the ED-CT group.

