The severity of, and improvement in the BDI-II scores within and between the groups will be examined using mixed-effects linear regression analysis with a random intercept and slope over time (four assessments: baseline, after sessions 4 and 8, post-treatment) and fixed effects for treatment assignment.) The 3-month follow-up data will be analyzed in a separate mixed-effects model. The main analysis will compare groups in terms of depression level (that is, diagnostic status and symptom intensity). Results on the other measures will be investigated in an exploratory manner. When analysis of secondary/other outcomes are performed, the error probability will be adjusted according to the number of group comparisons performed [98].

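### The stated BDI-II treatment effect averages in baseline, and no post-treatment or treatment-by-time contrast is named for the end-of-treatment primary outcome

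*Protocol article*

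**What the plan says.** All references are to the protocol article.

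- **Target.** Under Primary outcomes: "The level of depressive symptomatology and a categorical diagnosis of depression after treatment constitute the primary outcomes". Under Trial design, the hypothesis is that "the therapeutic gains will be larger in this condition than in the CT group at the completion of the therapy". Both point to the end of treatment.
- **Model.** Data collection, management, and analysis specifies a mixed model "with a random intercept and slope over time (four assessments: baseline, after sessions 4 and 8, post-treatment) and fixed effects for treatment assignment". Treatment assignment is the only fixed effect named, and baseline is one of the four outcome assessments. The purpose of the model is put this way: "The severity of, and improvement in the BDI-II scores within and between the groups will be examined using mixed-effects linear regression analysis".
- **Main comparison.** The same paragraph adds: "The main analysis will compare groups in terms of depression level (that is, diagnostic status and symptom intensity". It gives no time point.
- **Sample size.** The "planned main statistical test is ANOVA (repeated measures, between factors", with "effect size: 0.247; statistical power: 0.80", alpha 0.05, two groups, pre and post measurements and correlation 0.50, giving 100 participants. Simple randomisation produced 43 in CT and 57 in ED-CT.

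**The concern.** A fixed effect of treatment alone, fitted to repeated scores, estimates one arm difference held constant over all assessments. One of these is baseline, taken before any treatment, where the expected difference is zero. The coefficient is therefore pulled toward zero relative to the difference at the end of therapy. The sample-size test has the same feature, because a between-factors effect over pre and post is the group difference in the average of the two scores.

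If the analysis follows these two sections as written, a real end-of-treatment benefit could be reported at half its size or less, or missed. If the analysts meant something else, such as a difference in slopes or a difference at the last visit, the article does not say which. The choice of primary contrast then stays open until data are in hand.

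**Working it through.** **1. The plan's own figure.** For repeated-measures ANOVA, between factors, the noncentrality is lambda = f² × N × m / (1 + (m − 1) × rho).

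- With f = 0.247, N = 100, m = 2, rho = 0.50: lambda = 0.061009 × 200 / 1.5 = 8.13.
- F with 1 and 98 df gives power 0.806. N = 98 gives 0.798, so 100 is the smallest even total.
- The within-between interaction with the same f needs only N = 36.

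The stated 100 therefore comes from the group main effect averaged over pre and post.

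**2. What that test does if the difference exists only at post.** The standardised difference is d = 2f = 0.494. With 43/57, 1/43 + 1/57 = 0.0408.

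| Contrast | Effect (SD) | SE (SD) | Power |
|---|---|---|---|
| Pre/post average | 0.494 / 2 = 0.247 | √(0.75 × 0.0408) = 0.175 | 0.29 |
| Change (group-by-time) | 0.494 | √(2 × 0.5 × 0.0408) = 0.202 | 0.68 |
| Post, adjusted for baseline | 0.494 | √((1 − 0.25) × 0.0408) = 0.175 | 0.80 |

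The factor 0.75 in the first row is (1 + 0.5)/2. With 50/50 allocation the three powers are 0.29, 0.69 and 0.81. At correlation 0.50 the first and third contrasts have the same variance, so re-targeting needs no larger sample.

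**3. The four-assessment model, read literally.** Assumptions, because the article gives no variance components:

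- random intercept and slope, times 0, 1/3, 2/3, 1, with V the covariance of the four scores;
- 43/57, no dropout, covariance known;
- true post-treatment difference D = 0.494 post-treatment SDs.

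The treatment coefficient weights the four arm differences by w = V⁻¹1 / (1ᵀV⁻¹1), with SE = √(0.0408 / 1ᵀV⁻¹1). These weights do not depend on how a common time trend is coded. Power is Φ(z − 1.96) + Φ(−z − 1.96), with z = effect/SE.

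Worked case: intercept variance 70, slope variance 60, covariance −30, residual 30. The SD is 10 at baseline and at post, the baseline-post correlation is 0.40, and D = 4.94.

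- All four weights are 0.25 and SE = 1.597.
- Linear separation (0, 1/3, 2/3, 1): recovers 0.50; z = 2.47/1.597 = 1.55; power 0.34.
- Full separation by session 4 (0, 1, 1, 1): recovers 0.75; z = 3.705/1.597 = 2.32; power 0.64.
- Baseline-adjusted post contrast: conditional variance 100 − 40²/100 = 84; SE = √(84 × 0.0408) = 1.851; z = 2.67; power 0.76; recovers 1.00 under either pattern.

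The same formulas for several covariances:

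| Intercept var, slope var, covariance, residual var | Linear: recovered (power) | Early: recovered (power) | Adjusted post contrast: power |
|---|---|---|---|
| 70, 60, −30, 30 | 0.50 (0.34) | 0.75 (0.64) | 0.76 |
| 50, 0, 0, 50 | 0.50 (0.34) | 0.75 (0.64) | 0.81 |
| 50, 25, 0, 50 | 0.39 (0.26) | 0.65 (0.58) | 0.78 |
| 50, 50, 0, 50 | 0.32 (0.21) | 0.59 (0.56) | 0.76 |
| 50, 50, 0, 30 | 0.26 (0.15) | 0.53 (0.46) | 0.80 |

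Other covariances move the last column by a few hundredths, to about 0.74 at the low end. Larger slope variances (twice the intercept variance) push linear-separation recovery down to 0.13-0.18. The ranges are illustrations, not bounds.

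**The case against.** The strongest reply is that the model sentence is shorthand. It names no fixed time effect either, so nobody would fit it word for word. It says the model examines improvement between groups, which ordinarily means a group difference in change over time. It does not exclude treatment-by-time. A journal article may leave interaction terms and contrasts to an analysis plan that is not shown here. A linear model with that interaction, evaluated at post-treatment, recovers the full difference if separation is linear.

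Much of this stands: an interaction may well be intended, and omission alone would be no finding. What remains is that the article does specify the model and the main test, and both name a group effect that includes baseline. The sample size reproduces only on that reading.

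Two stronger conclusions might be drawn, and the document supports neither.

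- *That a linear-time model wastes power.* The article states no fixed linear time term. In the worked case the slope coefficient has power 0.63, but the post-treatment difference from the same linear model has 0.73, against 0.76 for categorical time with a common baseline. Linearity is still an assumption: if separation is complete by session 4, that linear contrast overstates the difference by 20%. This is an ordinary modelling trade-off.
- *That the follow-up analysis discards earlier scores.* The article says "The 3-month follow-up data will be analyzed in a separate mixed-effects model", but not which assessments enter that model.

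**Conclusion.** The point holds as a mismatch between the stated treatment effect and the stated outcome, not as proof that the intended analysis is wrong. As written, the model and the sample-size test give an effect diluted by baseline, and no contrast ties the BDI-II result to the end of treatment.

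Under the assumed covariances, a true difference of 0.494 SD and no dropout:

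- Literal effect, linear separation: roughly 25-50% recovered, power about 0.15-0.34.
- Literal effect, separation by session 4: about 53-75% recovered, power about 0.46-0.64.
- Baseline-adjusted post-treatment contrast: full recovery, power about 0.74-0.81.

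The direction of the dilution follows from including baseline. Its size depends on covariances and a separation pattern that the article does not give.

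**What to change.** In Data collection, management, and analysis, state that the primary BDI-II estimate is the treatment contrast at post-treatment. Take it from a model with treatment-by-time, preferably with categorical time, and with baseline BDI-II as a covariate or a baseline mean common to both arms.

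In Sample size, name the same contrast as the main test. With the article's own inputs, 100 participants give it power of 0.81 at 50/50 and 0.80 at 43/57, before dropout.

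Taking the 3-month contrast from the same model is optional.

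The cost is a change of wording and a few more parameters. Every assessment needed is already scheduled.

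### The BDI-II model names treatment as its only fixed effect, so its treatment coefficient does not estimate the end-of-therapy difference in gain that the trial hypothesises

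*Protocol article*

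**What the plan says.** In the protocol article, the section Data collection, management, and analysis opens the analysis paragraph with its aim: "The severity of, and improvement in the BDI-II scores within and between the groups will be examined". The model follows in the same sentence, a mixed-effects linear regression "with a random intercept and slope over time (four assessments: baseline, after sessions 4 and 8, post-treatment) and fixed effects for treatment assignment". Baseline is therefore one of the modelled outcomes, time appears only as a random slope, and treatment assignment is the only fixed effect named. Follow-up goes into a separate model.

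The Trial design section states the hypothesis for ED-CT: "the therapeutic gains will be larger in this condition than in the CT group at the completion of the therapy". The Abstract and the Primary outcomes section also place the primary outcomes after treatment.

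The Sample size section describes a different procedure: "planned main statistical test is ANOVA (repeated measures, between factors", with "two groups, two main measurements (pre-intervention and post-intervention" and an assumed correlation of .50 between them.

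**The concern.** A treatment effect without a treatment-by-time term is a single vertical shift between the arms, assumed equal at every assessment. At baseline the true shift is zero because patients are randomised. The hypothesis says the shift is present when therapy ends. The fitted coefficient is a weighted average of those differences, so a real difference in improvement is diluted by the baseline zero and partly absorbed by the random slopes.

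The BDI-II score is a primary outcome of a superiority trial. An analyst who followed the sentence in good faith could miss a real effect, or report the coefficient as the end-of-therapy difference when it is smaller. The gap also leaves the choice between main effect, slope and endpoint contrast open until the data are seen.

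**Working it through.** **1. The plan's own sample size.** Inputs from the Sample size section: "effect size: 0.247; statistical power: 0.80; α error probability: 0.05", m = 2 measurements, ρ = .50. For the between-groups main effect, λ = f²Nm / [1 + (m−1)ρ] = 0.247² × 100 × 2 / 1.5 = 8.13. On 1 and 98 df the power is 0.806, and 100 is the smallest even N that reaches 0.80. For the group-by-time interaction the divisor is 1 − ρ. N = 36 then gives λ = 0.247² × 36 × 2 / 0.5 = 8.79, which is already enough. So N = 100 reproduces as a group main effect averaged over pre and post, and not as an interaction.

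**2. What the stated coefficient estimates.** Scale time as t = (0, 1/3, 2/3, 1). With covariance V = ZDZ′ + σ²I, the coefficient averages the four arm differences with weights w = V⁻¹1 / (1′V⁻¹1).

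- Linear divergence from zero: share of the final difference recovered = (0.5·σ²/S − D12) / (D22 + σ²/S), where S = Σ(t − 0.5)² = 0.556.
- Full separation by session 4: share = 1 − w₀, which equals 0.30 + 0.9 × (linear share).

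**3. Assumed inputs, none of them in the documents except r and the arm sizes.** Residual variance σ² = 25, so σ²/S = 45; pre-post r = .50; 43/57 patients; no dropout; mean trend removed by a fixed time term. Then D11 = SDpre² − 25, D12 = 0.5·SDpre·SDpost − D11, and D22 = SDpost² − 25 − D11 − 2·D12.

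Example, SDs 8 and 11: D11 = 39, D12 = 44 − 39 = 5, D22 = 121 − 25 − 39 − 10 = 47. Linear share = (22.5 − 5) / (47 + 45) = 17.5/92 = 0.19. Weights are 0.53, 0.34, 0.16 and −0.03.

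| SD pre/post | Ratio | Linear share | Full by session 4 |
|---|---|---|---|
| 10/14 | 1.40 | 27.5/151 = 18% | 46% |
| 8/11 | 1.38 | 17.5/92 = 19% | 47% |
| 9/11 | 1.22 | 29/98 = 30% | 57% |
| 10/10 | 1.00 | 47.5/95 = 50% | 75% |
| 11/10 | 0.91 | 63.5/106 = 60% | 84% |

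At equal SDs the weights are 0.25 each. At 11/10 they favour post-treatment.

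**4. Power for a linearly growing difference of 0.5 post-treatment SD.** A plain post-treatment comparison has z = 0.5/√(1/43 + 1/57) − 1.96 = 0.515, which is power 0.70 throughout. For the other two tests:

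| SD pre/post | Treatment coefficient, no interaction | Treatment-by-time slope |
|---|---|---|
| 8/11 | 0.11 | 0.81 |
| 9/11 | 0.17 | 0.79 |
| 10/10 | 0.32 | 0.72 |

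**5. The literal model, with no fixed time term.** The average improvement must then be carried by the random slopes. As an approximation, an assumed mean fall of 14 points adds 14² = 196 to D22. The linear share becomes 17.5/(92 + 196) = 6% at SDs 8/11 and 63.5/(106 + 196) = 21% at 11/10. Leaving time out makes the dilution worse.

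**The case against.** The strongest reply is that the sentence shows its own intent. Improvement between groups is a treatment-by-time comparison, and improvement within groups needs a fixed time effect. Neither is listed, so the list may be shorthand in a condensed article whose full analysis plan is not shown. The Abstract and the Primary outcomes section do fix the time of interest after treatment. This stands as evidence of what the authors may have meant. It does not put the term into the model. The article did not leave the model to another document: it spells out the random effects, the assessments and the fixed effect, and the result does not serve its stated aim. The power calculation also points to a main effect. That is a two-measurement ANOVA and not this mixed model, so it makes the main-effect reading realistic without proving it.

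Second, the size is not in the documents. This stands. A reader might infer that a random slope always tilts the weights towards baseline, or that a fixed fraction such as 20-50% is lost. Neither follows. With fixed time in the model, the tilt needs variance that rises over time. Entry at BDI above 13 makes that plausible by truncating baseline scores, but it remains an assumption. With equal SDs there is no tilt, and with falling variance it reverses. A wider grid of variance components under linear divergence gives shares from about −10% to 80%.

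Third, a reader might go on to fault straight-line time, the covariance structure or bias from unequal dropout. Those points would need invented mean profiles and dropout rates, or are matters of preference. The documents do not support them as findings.

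**Conclusion.** The point holds as a mis-specified model statement. The single stated fixed effect does not estimate the between-group improvement promised in the same sentence, or the larger gain at completion of therapy. In every case worked above it understates a real end-of-therapy difference and, where power was calculated, has less power than a plain post-treatment comparison.

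The direction follows from including baseline without an interaction. The degree is conditional on the assumed SDs, r = .50, 43/57, no dropout and the shape of divergence: about 20-60% recovered under linear divergence and about 46-84% under early separation with a fixed time term, and less without one. The documents do not show that the authors will in fact omit the interaction. They show only that the stated model does.

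**What to change.** In Data collection, management, and analysis, rewrite the model sentence so that the fixed effects are time (assessment), treatment and treatment-by-time. Name the model-based treatment difference at the post-treatment assessment, and not the treatment main effect, as the primary BDI-II estimate and test. Adding a fixed time term alone is not enough, because the shares in step 3 already assume one.

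Whether time is a factor or linear, and which covariance structure is used, is the trial statistician's choice, to be fixed before unblinding. The cost is one sentence, with no new data and no change to trial conduct. Factor coding loses some power if the arms truly diverge in a straight line.
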